
### 2.7. Control group

The control group will receive usual care and the American Heart Association (AHA)’s “Answers by Heart” fact sheets. Answers by Heart is a series of downloadable patient information sheets, which include information about monitoring body weight, blood pressure, and cholesterol, as well as general tips for cooking healthfully and engaging in physical activity [39].

### 2.8. Post-intervention visit

After 12 weeks of the intervention, all participants will be invited to an in-person visit at week 13. During the visit, all the above parameters will be re-measured by the same RA and all the above survey questionnaires will be completed. All participants will then wear the activPAL3 and the CGM for another 7 days to examine their post-intervention activity and glycemic control. They will return the devices via pre-paid mail. To enhance adherence to the protocol, all participants will receive $50 for the post-intervention visit, and an additional $50 for mailing the devices back to the study team (a total compensation = $150 per participant). A subsample of participants from the intervention group (n = 20) will be invited to participate in an exit interview.

### 2.9. Primary outcomes

#### 2.9.1. Feasibility and acceptability

Feasibility will be determined by analyzing dropout rates and intervention compliance. The dropout rate will be calculated as the percentage of participants who withdrew consent. Participants who drop out will explain their reasons. For compliance, we will confirm if over 75% of participants wore their Fitbit for at least 5 valid days each week (with a valid day being over 10 hours of wear) for 75% of the study duration (9 weeks), and if the Sit Less group responded to 80% of goal-setting texts. These criteria are derived from metrics used to assess the feasibility of consumer-based wearable physical activity trackers in other digital behavior change studies [40].

Acceptability will be assessed through two satisfaction questionnaires and exit interviews. Due to the absence of a standardized satisfaction questionnaire for multi-technology interventions, we merged two questionnaires to assess overall satisfaction with the Sit Less program and its individual components (Fitbit, Fitbit app, Fitbit’s Move Alert, smart water bottle, and text messages). Satisfaction with the overall program and each technology (Fitbit, Fitbit app, Fitbit’s Move Alert, smart water bottle) will be measured using modified items from Lyons et al.’s questionnaire [41]. Satisfaction with the overall program will be evaluated with six items like “I would recommend the program” and “The program is likely to reduce sedentary behavior.” Additionally, the perceived ease and continued intention to use each technology component will be evaluated with 11 items such as “I found the Fitbit/Fitbit app/Smart water bottle convenient to use.” and “I would continue to wear the Fitbit”. A separate questionnaire by Burner et al. [42] will assess the text messaging component, evaluating the relevance of the message contents to the participants, as well as the frequency, motivation, and timing of the messages. All responses will be made on a Likert-type scale from 1 (strongly disagree) to 5 (strongly agree). Our threshold for acceptability outcomes is established so that at least 75% of participants must either agree or strongly agree with each statement on the satisfaction questionnaires [42].

In addition to the satisfaction questionnaires, an exit interview (n = 20) will be conducted by the PI or trained research staff and audio-recorded. For the exit interview, we will develop a semi-structured interview guide and thematic analysis. The interview guide will be structured to capture additional feedback on the acceptability and satisfaction of the intervention, barriers and facilitators to sedentary behavior reduction, and perceived health impacts of sedentary behavior reduction.

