### 2.13. Analysis plan

Feasibility (dropout rates and intervention compliance) and acceptability outcomes (assessed by satisfaction questionnaires) will be calculated and reported as percentages. The determination of whether the Sit Less program is feasible and acceptable will be based on the previously defined criteria. The recorded exit interview will be transcribed verbatim and analyzed using a thematic approach to guide refinements to future sedentary behavior reduction interventions as well as to identify barriers and facilitators to sedentary behavior reduction. To enhance credibility, we will follow the consolidated criteria for reporting qualitative research (COREQ) guidelines [54].

For sedentary behavior and light PA data from the activPAL 3, we will only include data of daily wear time >10 hours, with a minimum of 4 valid days [37]. The activPAL data will be downloaded and analyzed by using the activPAL 3 processing software and applying “CREA (enhanced analysis algorithm)” processing setting (PAL analysis, V8.11, PAL Technologies). The CREA algorithm demonstrated excellent agreement with diary data [55] and strong correlation with using a traditional algorithm to assess wake time activities [56].

Once all the data from activPAL 3 have been processed, statistical analyses will be conducted using STATA 18 (StataCorp, U.S.A). All analyses will adhere to an intention-to-treat approach, and there will be no imputation of data. Given this simple pre-post design, participants in both study groups without a post-intervention value for a respective outcome measure will not be included in the analysis of effects on that measure. Demographic and other baseline values will be compared between those who do and do not complete the study to inform potential modifications to the intervention for future studies. Descriptive statistics will summarize the demographic and clinical characteristics of the participants. Chi-Square, Mann-Whitney or independent *t*-tests will be used to inform potential differences between control and intervention groups at baseline. We will consider sex as a biological variable and conduct subgroup analyses to determine if there are differences in sedentary behavior outcomes and the acceptability of the Sit Less program.

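### Dropout, half of the primary feasibility outcome, counts only formal withdrawal of consent, so silent losses count as retained, and no stated criterion carries the rate into the feasibility verdict

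*Protocol article*

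**What the plan says.** Section 2.9.1 lists feasibility among the primary outcomes and names its two parts: "Feasibility will be determined by analyzing dropout rates and intervention compliance". The first part has an operational definition: "The dropout rate will be calculated as the percentage of participants who withdrew consent". The next sentence expects those who drop out to give their reasons, which presupposes someone still in contact.

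The same section attaches numerical marks to the other elements:
- Fitbit wear: "we will confirm if over 75% of participants wore their Fitbit for at least 5 valid days each week", sustained for 9 weeks.
- Text response: "if the Sit Less group responded to 80% of goal-setting texts".
- Acceptability: "at least 75% of participants must either agree or strongly agree with each statement".

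No mark is attached to dropout.

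Section 2.13 says how these are used. The reporting rule is "Feasibility (dropout rates and intervention compliance) and acceptability outcomes (assessed by satisfaction questionnaires) will be calculated and reported as percentages". The decision rule is "The determination of whether the Sit Less program is feasible and acceptable will be based on the previously defined criteria". The same section leaves participants without a post-intervention value out of the analysis of that outcome, without imputation. It also plans a baseline comparison of completers with non-completers.

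**The concern.** The definition captures one route out of the study, the formal one. In a 12-week home-based programme with a single in-person follow-up visit, a participant can also leave by not answering and not attending. Such a person has no week-13 assessment and is not analysed, yet does not count towards dropout. The plan thus treats the same person as missing for the efficacy analysis and as retained for the feasibility outcome.

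This matters because section 2.2 justifies the sample size by the need to find feasibility problems and to inform future research. Retention to the follow-up assessment is one of the main quantities that a later trial takes from a pilot, both to judge whether the design works and to inflate its sample size.

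The second part concerns the decision. Section 2.13 points back to defined criteria, and for dropout there is nothing to point back to. A reader cannot tell whether dropout is meant to count towards the verdict.

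**Working it through.** **The plan's own figure.** The article states no dropout rate or limit, so there is none to reproduce. The nearest stated figure is the sample-size basis in section 2.2: n = 30 to detect, with 95% confidence, a problem of 10% probability. The formula is n = ln(1 − 0.95)/ln(1 − 0.10) = 28.43, rounded up to 29. That agrees with 30 for practical purposes and is not in dispute.

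**Size of the understatement.** Let N be the number randomised, w the number who withdraw consent, and l the number lost without withdrawing.
- Rate under the article's definition: w/N.
- All-cause rate: (w + l)/N.
- Gap: l/N.

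N = 70 comes from section 2.2; the dropout sentence does not limit itself to one arm. The values of w and l are assumptions, because the article gives neither. Each silent loss is worth 1/70 = 1.4 percentage points.

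| w (assumed) | l (assumed) | Article's rate | All-cause rate (exact 95% CI) | Gap, points |
|---|---|---|---|---|
| 2 | 0 | 2/70 = 2.9% | 2/70 = 2.9% (0.3 to 9.9%) | 0 |
| 2 | 7 | 2/70 = 2.9% | 9/70 = 12.9% (6.1 to 23.0%) | 10 |
| 2 | 14 | 2/70 = 2.9% | 16/70 = 22.9% (13.7 to 34.4%) | 20 |
| 0 | 14 | 0/70 = 0% | 14/70 = 20.0% (11.4 to 31.3%) | 20 |

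**What follows if a later trial relies on the reported rate.** Inflating by 1/(1 − w/N) instead of 1/(1 − (w + l)/N) leaves the later trial short by a fraction 1 − (N − w − l)/(N − w) = l/(N − w). With w = 2 this is 0/68 = 0%, 7/68 = 10.3% and 14/68 = 20.6% for l = 0, 7 and 14. It applies only if planners use that rate and not the numbers analysed.

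**Routes into the verdict.**
- *Dropout rate itself:* it has no threshold, so no value of it is stated to fail the feasibility criterion.
- *Control arm:* section 2.7 gives this group usual care and fact sheets. It receives no Fitbit and no goal-setting texts, so its losses cannot appear in the compliance criteria either.
- *Sit Less arm:* a participant who goes silent stops producing Fitbit days and text replies. If all 35 stay in the denominator, passing needs more than 75%: 26/35 = 74.3% fails and 27/35 = 77.1% passes. Nine early losses would therefore fail the Fitbit criterion (35 − 9 = 26). The article does not state that denominator. A participant who complies for 9 weeks and then misses week 13 would pass the Fitbit criterion in any case.

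**The case against.** Several points on the other side have force.

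- **Attrition can reach the verdict.** A reader might infer that no amount of loss could make the programme infeasible. The documents do not support that. Early Sit Less losses can fail the Fitbit or text criterion, and the intention-to-treat statement in section 2.13 favours keeping them in the denominator. What stands is narrower: the dropout rate and control-arm losses have no stated route.
- **Losses will be visible elsewhere.** A reader might infer that the trial would conceal its attrition. That is not supported either. Section 2.1 commits to CONSORT, section 2.13 compares completers with non-completers, and the numbers analysed will differ from those randomised. This limits the harm, but it does not correct the defined primary-outcome figure or link those losses to the decision.
- **Invalid wear is not dropout.** After the week-13 visit participants wear the activPAL for 7 days, and "They will return the devices via pre-paid mail". Someone who attends and then returns fewer than 4 valid days, or no device, has been retained; the failure is one of measurement. Section 2.14.1 checks returned data and provides for measures to be retaken. This objection is right, and the two quantities should be kept apart.
- **No pass mark may be deliberate.** A descriptive dropout rate beside thresholded compliance criteria is a common pilot design, and the article condenses a fuller protocol. Taken alone, the missing mark would be a weak point. The narrow definition is different: it is stated in the article, not left out of it.

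**Conclusion.** The point holds, and the definition carries it. Followed as written, the dropout rate understates all-cause attrition by l/N. The article does not let that be computed: it is zero if nobody is lost silently, and reaches 20 percentage points at an assumed 14 silent losses of 70. In addition, the verdict refers to criteria of which none exists for dropout, so the dropout rate, and control-arm loss in particular, has no stated place in it.

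The conclusion assumes only that some participants may leave without withdrawing consent, which section 2.13 itself anticipates by providing for missing post-intervention values. It does not show that attrition will be large, and it leaves the efficacy estimates unaffected. Severity: should-fix.

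**What to change.** 1. Define dropout as the percentage of all randomised participants without the week-13 assessment for any reason. Report it by arm and by reason (consent withdrawal, loss to follow-up, missed visit), with consent withdrawal as a sub-category.
2. Report separately the percentage without valid post-intervention activPAL data, using the 4-valid-day rule already in section 2.13.
3. Either state a retention criterion in advance, at a value that the sponsor chooses, or say that dropout is descriptive and not part of the feasibility verdict. Section 2.14.1 has the study team monitoring dropout throughout, so a criterion set after losses are known would not count as pre-specified. In that case the descriptive option is the cleaner one.

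The cost is a change of wording. Attendance and device validity are already tracked, so no new data are needed. The reported dropout figure may be less favourable than under the present definition.

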#### 2.6.2. Instructional goal setting session

The PI will provide an instructional goal setting session during Baseline Visit 2. The PI will review the prior 7 days of activPAL3 data and identify targetable prolonged sedentary bouts with the participant. The PI and the participant will set two goals: 1) a sedentary behavior reduction goal aimed at reducing daily sedentary time gradually until they reach the goal of ≥ 120 minutes of sedentary time reduction; and 2) a sedentary break goal of 5 minutes of standing/walking every 1 hour and then increasing its duration to 10 minutes and frequency of the sedentary break to every 30 minutes [35]. These goals have been demonstrated to be feasible in stroke patients and CVD patients [8, 21]. Participants will have the autonomy to set their weekly goals, whether to maintain the same target as the previous week, or reduce sedentary time. We do not recommend reducing sedentary time by more than 30 minutes per week, but adjustments can be made based on the participants’ current sedentary hours and willingness.

In addition, the participant will be given the Ten Top Tips (TTT). The TTT is a booklet developed from the Habit Formation Theory and includes tips to add sedentary breaks into their daily routine [36]. The original TTT booklet [36] was obtained from [name] [36], one of the developers of the Habit Formation theory [31], and it was applied to sedentary behavior with permission to revise it for the current study. The original TTT booklet suggested limiting TV watching to no more than one hour at a time and promoting light physical activities such as walking—by leaving the remote control by the TV, standing up during commercials, opting for stairs, and parking at a distance from the entrances of malls or offices [36]. It also included recommendations for stretching and muscle strengthening exercises [36]. We revised the original TTT booklet to include 8 tips, excluding the stretching and muscle training recommendations and incorporating the Fitbit and smart water bottle into daily routines. Although the suggested tips involve only light levels of physical activity, such as standing and walking for 3 to 5 minutes every hour—activities with no more risk than those encountered daily—we will instruct participants to stop these exercises immediately if they feel unwell or experience discomfort, and to promptly seek medical advice.

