### 2.12. Data management plan

Study participants will complete questionnaires online via REDCap, and the study team will review the responses in the presence of the participants to clarify or complete any missing information. REDCap, a secure, HIPAA-compliant web-based application developed at Vanderbilt University, will be used to manage all data. It provides data entry, audit trails, and export procedures, and flags inconsistent or out-of-range responses for review.

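### The acceptability rule needs 75% agreement on every statement in at most 35 people, so it often fails a program moderately above the bar, and staff review of answers risks favourable responses.

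*Protocol article*

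**What the plan says.** Acceptability is part of the primary outcome. Section 2.9.1 of the protocol article sets the bar: "at least 75% of participants must either agree or strongly agree with each statement on the satisfaction questionnaires". The statements come from two merged questionnaires:

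- Overall program: "Satisfaction with the overall program will be evaluated with six items".
- Technologies: "the perceived ease and continued intention to use each technology component will be evaluated with 11 items".
- Text messages: a separate instrument, "evaluating the relevance of the message contents to the participants, as well as the frequency, motivation, and timing of the messages", with no item count given.

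Section 2.13 says that the feasibility and acceptability outcomes "will be calculated and reported as percentages", and that the decision on whether the program is feasible and acceptable rests on the criteria already defined. The article does not say who forms the denominator of the acceptability percentage. Section 2.2 puts 35 people in the intervention group.

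Section 2.12 has participants fill in questionnaires online, after which "the study team will review the responses in the presence of the participants to clarify or complete any missing information". The satisfaction questionnaires are not exempted.

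**The concern.** A bar that each of many statements must clear is much harder to pass than the same bar on one statement. With 35 respondents, each observed percentage carries a wide margin. A program whose true agreement is above 75% throughout can be declared unacceptable because one statement fell short by chance. One unpopular component could do the same to the whole program.

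The second issue is measurement. Satisfaction answers are open to social desirability, and going over them face to face with the team running the study is a setting where that can happen. At stake is a pass/fail statement on a primary outcome that is meant to inform a later large trial.

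**Working it through.** **The plan's own figure.** The article gives no operating characteristics for the 75% rule, so there are none to reproduce. Its only related figure is the sample-size basis in section 2.2: 30 people to see a problem of 10% probability with 95% confidence. The check is ln(0.05)/ln(0.90) = 28.4, so 29 people, and 30 give 1 − 0.90^30 = 95.8%. The stated figure reproduces. It concerns seeing a problem at least once, which is a different question from clearing a 75% bar.

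**Inputs from the article.** The bar is 75% on each statement (2.9.1). The maximum number of respondents is 35 (2.2). The items stated outright are 6 + 11 = 17 (2.9.1).

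**Assumptions.**
- One item per named text-message topic adds 4, giving 21. The article does not give this count.
- True agreement is the same on every item, at 70% to 90%.
- Correlation between items within a person runs from 0 to 0.9, modelled by a one-factor Gaussian copula (20,000 simulated trials per setting).
- All 35 respond.

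**Passing count.** 0.75 × 35 = 26.25, so 27 of 35 (77.1%) must agree on every statement.

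**One statement.** P(X ≥ 27), with X binomial(35, p), is 0.234 at p = 0.70, 0.745 at 0.80, 0.931 at 0.85 and 0.994 at 0.90.

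**All statements.** Under independence this is the one-statement probability raised to the number of items. At 85%, 0.9311^17 = 0.30 and 0.9311^21 = 0.22. With correlation, by simulation:

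| True agreement | Items | Corr. 0 | 0.5 | 0.9 |
|---|---|---|---|---|
| 70% | 17 | <0.001 | 0.001 | 0.03 |
| 70% | 21 | <0.001 | <0.001 | 0.02 |
| 80% | 17 | 0.007 | 0.12 | 0.36 |
| 80% | 21 | 0.002 | 0.10 | 0.34 |
| 85% | 17 | 0.30 | 0.50 | 0.72 |
| 85% | 21 | 0.22 | 0.45 | 0.70 |
| 90% | 17 | 0.90 | 0.92 | 0.96 |
| 90% | 21 | 0.88 | 0.90 | 0.95 |

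The wording on the 11 technology items could also mean 11 per technology. With four technologies that is 6 + 44 + 4 = 54 items, and at 85% under independence 0.9311^54 = 0.02.

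**Precision of one percentage.** The exact (Clopper-Pearson) 95% interval for 27/35 is 59.9% to 89.6%.

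**Denominator.** If 20% did not respond (assumed), 28 would remain. Then 21/28 = 75% meets the bar on a statement, while 21/35 = 60% of those allocated agreed. At 10% non-response, 24/32 = 75% against 24/35 = 69%.

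**The case against.** The strongest reply is that strictness suits this pilot. Section 2.2 disclaims hypothesis testing and sizes the study to find problems. Section 2.9.1 deliberately examines each component, and a bar on each statement exposes a disliked one. A clearly well-liked program, at 90% agreement or more, usually passes. Replacing the rule by a single overall bar would have its own cost: one 75% bar passes with probability 0.23 when true agreement is 70%, against under 0.03 for the present rule. All of this stands. It is a reason to keep the item-level bar as a flag; it does not justify letting one missed statement decide the whole verdict.

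It can also be said that the stated purpose of the staff review is clarification and completeness, and that section 2.12 is general. That is fair. Influence on answers is a plausible risk, not a documented fact.

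A reader might infer three stronger points that the article does not support:

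- **That the rule flatters a poor program.** By sampling error it does not, as the 70% rows show. Flattery would need response bias or non-response of a size the article does not give.
- **That completers are the stated basis.** The exclusion of people without a post-intervention value in section 2.13 concerns the analysis of effects. The acceptability denominator is simply not given, and a condensed article may leave it to a fuller document.
- **That the interviewer affects the 75% verdict.** The investigator delivers the goal-setting session ("The PI will provide an instructional goal setting session during Baseline Visit 2"), and the exit interview "will be conducted by the PI or trained research staff and audio-recorded". But interviews carry no threshold and are analysed thematically.

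**Conclusion.** The point holds in a limited form. Read plainly, sections 2.9.1 and 2.13 let one statement below 75% fail the whole program. If true agreement is 85% throughout, the chance of that failure is about 28% to 78% (1 − 0.72 to 1 − 0.22). At 90% it is about 4% to 12%. Agreement rates, correlations and the 21-item count are assumptions, but the conclusion at 85% also holds with only the 17 stated items. A percentage that just clears the bar, 27/35, is compatible with true agreement from 60% to 90%, so the bare percentage says little about which side of 75% the truth lies on. The errors run mainly one way: false failure is common moderately above the bar, and false passing is rare below it.

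Separately, face-to-face review of satisfaction answers is an avoidable risk of favourable responding. Its size cannot be estimated from the article.

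**What to change.** 1. Collect the satisfaction items privately by REDCap link, with required fields, and exempt them from the staff review of answers in section 2.12. Required fields serve the completeness purpose of that review.
2. Report every feasibility and acceptability percentage with an exact 95% confidence interval, and read the 75% bar alongside it.
3. Add a sensitivity analysis over all participants allocated to the intervention, counting non-responders as not agreeing. Dropout is already a separate feasibility measure, so this belongs beside the main figure and does not replace it.
4. State that a statement below 75% flags that component for refinement and does not by itself make the whole program unacceptable.

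The cost is wording and a REDCap setting, with no extra participants, visits or staff. The downsides are a few answers left unclarified and a less clear-cut verdict.
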